# 7. Safety Assessment

# 7.1. Definition of Adverse Event：

- Adverse events (AE): AE refers to any adverse medical events occurring in this clinical experiment from the moment that the patient signs the informed consent and is chosen to participate in this study to the last follow-up, whether or not the events are caused by the use of the medicine described.

# 7.1.2. Criteria on severity of adverse events:

All adverse events during this clinical study should be recorded in Adverse Event Page of CRF. The severity of adverse events is classified with a uniform standard:

Mild With perceptible discomfort but not affect daily activity

Moderate With marked discomfort that affects daily activity

Severe Unable to work or perform daily physical activity without discomfort

Severity is a measure of intensity. An AE of severe intensity need not necessarily be considered as serious adverse events (SAE). For example, as headache may be severe on the intensity, but cannot be regarded as SAE, unless meeting SAE criteria.

# 7.1.3. Adverse events of interest

The causal judgment between all adverse events and study drugs should be determined and classified by five grades: affirmative relevance, probable relevance, possible relevance, suspected relevance and impossible relevance. The former three are regarded as adverse drug reaction (ADR).

The following factors should be considered:

1. Whether or not there is logical connection between the initiation of medicine treatment and the appearing time of suspected ADR (usage of drug);
2. Whether or not the suspected ADR is related to other known medicine (accord with literature and/or drug instruction);
3. Whether or not the suspected ADR could be explained by the patient’s pathological situation, combined medication, combined or former therapy, etc. (other explanation);
4. Whether or not the suspected ADR is alleviated or disappeared after the drug withdrawal or dose reduction (withdrawal remission);
5. Whether or not the same reactions reoccur after the patient taking the suspected medicine again (reoccur after reuse);

Researchers should evaluate possible associations between adverse events and study drug and combined drug; with reference to the following table:

| Consideration | Usage of drug | Consistent with literature | Other explanation | Withdrawal remission | Reoccur after reuse |
| --- | --- | --- | --- | --- | --- |
| Affirmative relevance | ＋ | ＋ | － | ＋ | ＋ |
| Probable relevance | ＋ | ＋ | － | ＋ | ？ |
| Possible relevance | ＋ | ＋ | ± | ± | ？ |
| Suspected relevance | ＋ | － | ± | ± | ？ |
| Impossible relevance | － | － | ＋ | － | － |

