# 3.4 Adverse drug reaction

Adverse reactions to test drugs are not known. The National Adverse Reaction Monitoring Database showed the possible reactions might included gastric discomfort such as nausea, bloating, and hiccups, etc.

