# 7.2.1 . Definition on specificity of serious adverse events

In this study, the following events will not be reported as serious adverse events unless they are judged negative and the researcher believes that it is related to the study drug

- Cardiovascular death
- Re-hospitalization for heart failure
- Given up treatment due to worsening heart failure
- Successful resuscitation after cardiac arrest
- Malignant arrhythmia
- Non-fatal stroke

Other events leading to fatal outcomes should be reported as serious adverse events.

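### The causality grid makes agreement with existing literature a condition for every ADR grade, so applied as written it keeps previously undescribed reactions out of the ADR class

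*Protocol*

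**What the plan says.** Protocol Section 7.1.3 sets the causality rule: "The causal judgment between all adverse events and study drugs should be determined and classified by five grades". The grades are affirmative, probable, possible, suspected and impossible relevance, and "The former three are regarded as adverse drug reaction (ADR". Suspected and impossible relevance therefore fall outside the ADR class.

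Five factors feed the grade: timing, prior documentation, other explanations, remission on withdrawal, and recurrence on reuse. The documentation factor reads "Whether or not the suspected ADR is related to other known medicine (accord with literature and/or drug instruction". A grid then gives each grade a pattern over the five factors, and researchers are told to use it as a reference.

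Section 3.4 describes the known reaction profile of the product: "Adverse reactions to test drugs are not known". It adds that a national monitoring database suggests gastric discomfort, with a few examples and an open ending.

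Section 9.2.4 compares the number and incidence of adverse events between arms and says that their relation to the drug will be analysed further.

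**The concern.** A long-term placebo-controlled trial is one of the better opportunities to find reactions that nobody has described. A definition that admits an event to the ADR class only if it has been described before works against that purpose. The evidence that should carry most weight for a new reaction is onset after dosing, no competing cause, resolution on stopping and return on restarting. Under this grid none of it can make up for the absence of a precedent.

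The protocol gives the drug almost no stated reaction profile, so the literature criterion could often be a minus. The protocol also expects events beyond gastric discomfort: Section 2.5 provides for allergic reactions clearly tied to the product, and Section 4.2 names volume depletion and renal events as adverse events of interest. Unless literature or the drug instruction covers them, the grid would keep such events out of the ADR class however strong the individual case. At stake is whether the trial's statements about drug-related events understate new harm.

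**Working it through.** The protocol states no figure to reproduce here, so the check is one of logic. The inputs are the five rows of the grid in Section 7.1.3:

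| Grade | Timing | Literature | Other explanation | Withdrawal remission | Recurrence on reuse | ADR? |
|---|---|---|---|---|---|---|
| Affirmative | + | + | − | + | + | yes |
| Probable | + | + | − | + | ? | yes |
| Possible | + | + | ± | ± | ? | yes |
| Suspected | + | − | ± | ± | ? | no |
| Impossible | − | − | + | − | − | no |

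**Step 1, compare rows.** Every ADR row has + under literature and every non-ADR row has −. Possible and Suspected agree in the other four columns. For an event at that boundary, prior documentation alone decides ADR status.

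**Step 2, enumerate.** Let timing, literature and other explanation be + or −, and let withdrawal and reuse be +, − or unknown. That gives 2 × 2 × 2 × 3 × 3 = 72 patterns, 36 for each value of literature. The grid does not say how ? and ± are to be read, so two readings were used. In the strict reading ? means unknown and ± means + or −. In the loose reading both mean any value.

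| | Strict | Loose |
|---|---|---|
| Literature +: patterns reaching an ADR grade | 5 of 36 | 18 of 36 |
| Literature −: patterns reaching an ADR grade | 0 of 36 | 0 of 36 |
| Literature −: patterns fitting no row | 31 of 36 | 17 of 36 |

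The strict 5 is Affirmative (1) plus Possible (2 × 2 × 1 = 4); the single Probable pattern lies within Possible. The loose 18 is Possible (2 × 3 × 3), which contains the other two rows. With literature −, the rows that fit are Suspected (4 strict, 18 loose) and Impossible (1), so 36 − 5 = 31 and 36 − 19 = 17 fit none.

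**Step 3, take the strongest case for a new reaction.** Plausible timing, no literature, no other explanation, remission on withdrawal and recurrence on reuse is + − − + +. In the strict reading it fits no row, because Suspected needs reuse to be unknown. In the loose reading it fits only Suspected. It is not an ADR in either. Change the literature cell alone to + and the same event is Affirmative, the highest grade.

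These are counts of patterns, not probabilities. The patterns are not equally likely, and the number of events affected depends on data that the protocol cannot give.

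**The case against.** The other side has several good points.

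- **The grid is guidance.** Researchers consult it when judging, and its failure to cover some patterns shows that it cannot be a complete algorithm. This stands, and it rules out saying that an undescribed reaction can never be called an ADR. But no exception is written, and an investigator who follows the grid reaches the wrong label.
- **The literature criterion is wider than Section 3.4.** It extends to literature and drug instruction generally, its English wording is loose, and the gastric list is open-ended. The background in Section 1.3 also reports diuretic and cardiotonic effects. A reader might infer that every reaction outside gastric discomfort is capped at Suspected. The documents do not support that, because other sources may supply the plus.
- **No ADR rate or ADR table is specified.** Section 9.2.4 refers to the relation with drugs for all adverse events and does not drop Suspected. A reader might infer that new reactions contribute zero to a planned ADR rate; the protocol describes no such output, and layout may be left to the SAP. What remains is the definition of an ADR, which the protocol itself fixes.
- **Safety data are otherwise protected.** All adverse events are recorded (Section 7.1.2) and compared between blinded arms (Section 9.2.4), so an unlisted reaction can still appear as an imbalance. SAEs are reported within 24 hours regardless of causality (Section 7.3). This stands and limits the consequence.
- **Section 7.2.1 is separate.** It exempts endpoint-type events from SAE reporting "unless they are judged negative and the researcher believes that it is related to the study drug". A reader might infer that the grid weakens this trigger. The condition turns on the researcher's belief and cites neither the grid nor the ADR class, and nothing says that a Suspected grade fails it. No effect is shown.

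**Conclusion.** The point holds within limits. As written, Section 7.1.3 makes literature agreement a necessary condition for the ADR label: none of the 36 patterns without it reaches an ADR grade under either reading, and the most convincing new reaction is either Suspected or unclassifiable. This is a stated rule that misclassifies, and not a detail left for the SAP.

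The effect is limited to ADR labelling and to the analysis of drug relation. It does not touch the primary endpoint, the recording of adverse events, the comparison of incidence between arms or the reporting of SAEs. It should be changed because the correction is cheap and safety is a stated objective.

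The conclusion assumes that investigators follow the grid, and that the documentation factor means agreement with literature or drug instruction, as its parenthesis and the column heading both indicate. That it will matter often is likely, given Section 3.4, but cannot be quantified from the protocol.

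**What to change.** Count Suspected relevance as an ADR in the safety analysis, and report ADRs with and without that grade.

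Alternatively, make literature agreement supportive only, so that its absence does not bar a higher grade. The boundary between Possible and Suspected must then be redefined, since nothing else separates them.

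In either case, state how ? and ± are to be read and how to grade a pattern that fits no row. Under the strict reading, counting Suspected would still miss the undescribed reaction with positive rechallenge.

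The cost is protocol wording and one further table. ADR counts will rise in both arms and become less specific: under the loose reading, half of the Suspected patterns (9 of 18) have another explanation present. Showing the result both ways lets the reader see this, and because grading is blinded the change applies alike to both arms. Nothing in patient management changes.

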# 7.2. Definition serious adverse events

 Significant adverse events (SAE) refer to any adverse event requiring pertinence medical measures (as withdrawal, dose reduction and symptomatic treatment) and hematologic abnormity and /or other laboratory abnormity.

An SAE is an AE occurring during any study phase (i.e., run-in, treatment, washout, follow-up), that fulfils one or more of the following criteria:

- Death
- At life-threatening condition (the patient with this event has risk of immediate death at the time of occurring events; but do not include the aggravation of events that can lead death)
- With required hospitalization or extended hospital stay
- Sustained or significant loss of productivity or disability
- Congenital malformation

Other condition that may jeopardize the patient or may require medical intervention to prevent one of the outcomes listed above can also be classified as SAE.

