# 4.2. Safety outcome measure:

- Adverse events (Serious Adverse Events [SAEs], Discontinuation of IP due to Adverse Events, etc.)
- AEs of interest (volume depletion, renal events, etc.)
- Clinical laboratory indexes: blood routine test (hemoglobin, red blood cells, white blood cells, platelets), routine urine test (urinary protein, urinary white blood cells, urine red blood cells), serum biochemistry (urea nitrogen, creatinine, blood uric acid, total protein, albumin, alanine aminotransferase, aspartate aminotransferase, alkaline phosphatase, total bilirubin, fasting blood glucose, potassium, sodium, chlorine, total cholesterol, triglycerides, low density lipoprotein, high density lipoprotein).
- 12-lead ECG
- Physical examination

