# 7.3. Recording of adverse events and follow-up

If any adverse events occurred, especially those associated with the study drug, should be followed up until the patients return to baseline or tend to stabilize. If the baseline status or stability cannot be restored after follow-up, it should be noted in the CRF. All SAEs have to be reported within 24 hours, whether or not considered causally related to the investigational product, or to the study procedure(s).

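### Section 7.2 gives the abbreviation SAE two different meanings, and the 24-hour reporting rule and a safety outcome both depend on it without saying which meaning governs.

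*Protocol*

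**What the plan says.** Section 7.2 of the protocol contains two consecutive statements, each of which fixes a meaning for SAE.

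- The first reads "Significant adverse events (SAE) refer to any adverse event requiring pertinence medical measures (as withdrawal, dose reduction and symptomatic treatment" and then adds "hematologic abnormity and /or other laboratory abnormity". The word expanded is significant, not serious. The laboratory part has no threshold and no requirement of clinical significance.
- The second reads "An SAE is an AE occurring during any study phase (i.e., run-in, treatment, washout, follow-up), that fulfils one or more of the following criteria". The list that follows is the familiar one: death, threat to life, hospital admission or a longer stay, disability, and congenital malformation. A closing clause allows other conditions that endanger the patient, or need intervention to prevent a listed outcome, to be classified as SAEs.

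Two other sections depend on the abbreviation. Section 7.3 states "All SAEs have to be reported within 24 hours, whether or not considered causally related to the investigational product". Section 4.2 names as a safety outcome "Adverse events (Serious Adverse Events [SAEs], Discontinuation of IP due to Adverse Events, etc". Section 4.2 expands the abbreviation as serious but does not point to either paragraph of 7.2. Section 7.3 does not expand it at all.

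**The concern.** A definition that triggers expedited reporting and also feeds an outcome table has to select one set of events. Here the opening sentence of 7.2 covers events that merely needed treatment, while the following paragraph covers events with serious consequences. Section 2.2 plans for more than 100 centres, so uniform classification should not depend on each site inferring which paragraph was meant.

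Two things are at stake. One is the reporting duty: a site that takes the opening sentence at its word would send treated, non-serious events within 24 hours. The other is the SAE comparison between arms, which would then be a mixture whose make-up depends on how each site read the page. A statistical analysis plan can decide how to tabulate SAEs, but it cannot change a site's reporting duty, and it would start from records that had already been classified differently at source.

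**Working it through.** No arithmetic applies, because the protocol states no figure on this point. The check is to compare the two definitions and then test each against the other uses of the term.

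**Step 1. Are the two definitions the same set?** The first definition has two possible readings, because the laboratory part is joined by *and*. On the additive reading, an event qualifies if it needed measures, and laboratory abnormalities qualify as well. On the conjunctive reading, an event must have needed measures and also involve a laboratory abnormality. Four test events:

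| Event | First definition, additive | First definition, conjunctive | Seriousness list |
| --- | --- | --- | --- |
| Nausea treated symptomatically, no serious consequence, laboratory values normal | SAE | not SAE | not SAE |
| Isolated abnormal laboratory value, no action taken | SAE | not SAE | not SAE |
| Abnormal laboratory value leading to withdrawal of study drug, no listed outcome | SAE | SAE | not SAE, unless the closing clause is invoked |
| Unplanned hospital admission for treatment of an infection | SAE | depends on laboratory findings | SAE |

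Neither reading of the first definition gives the same set as the list. Settling the *and* would therefore not remove the conflict. Treated nausea is a realistic test case: section 3.4 names nausea among the possible reactions to the product.

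**Step 2. Does any other text decide between them?** No section says which definition governs. Several do lean one way:

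- The heading of 7.2 speaks of serious events, as do sections 4.2 and 7.2.1.
- Section 7.1.2 separates intensity from seriousness: "An AE of severe intensity need not necessarily be considered as serious adverse events (SAE". Its headache example makes SAE status conditional on meeting the SAE criteria.
- Section 3.2.2 records SAEs, events leading to discontinuation and events of interest as separate categories, and section 4.2 also lists discontinuation because of an adverse event alongside SAEs. If withdrawal alone made an event an SAE, those separate entries would largely be redundant.
- Section 7.4 sends clinically significant laboratory findings that meet set conditions to the adverse event page. The first definition has no such filter.
- Section 7.2.1 exempts endpoint events, such as cardiovascular death and heart failure admission, from SAE reporting under stated conditions. That exemption fits naturally with a list built on seriousness.

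**Step 3. What follows for reporting and counting?** The seriousness list is also stated in 7.2, so a site that adds the first definition to it would over-report; the listed events would still be captured. Its SAE count would contain serious events plus treated non-serious events. A site that follows the list alone would report only the former.

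**Step 4. Can the effect be sized?** No. Neither the expected rate of adverse events, nor that of SAEs, nor the share of sites that would take the wide reading is given.

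**The case against.** The strongest reply is that the intended definition can be recovered. The heading, the expansion of the abbreviation in 4.2 and 7.1.2, and the separate handling of discontinuations and laboratory findings all point to the seriousness list, and experienced sites would probably follow it. This stands as far as intent goes, and it limits the claim to what sites could do. It does not cure the text: the competing sentence comes first, sits under the same heading and carries the same abbreviation. If significant events were meant as a separate category, sharing the abbreviation is itself the error.

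Three stronger conclusions that a reader might draw are not supported.

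- *Any laboratory abnormality is an SAE.* The joining word is *and*, and a conjunctive reading is possible.
- *Section 7.1.2 flatly contradicts the opening sentence of 7.2.* Its headache example is conditional on the SAE criteria and says nothing about treated headaches. It is in tension with the wide reading but does not contradict it.
- *The SAE comparison will be diluted by a known amount.* Any such figure rests on invented rates. Assume, purely for illustration, serious events in 15% of control patients, a true risk ratio of 1.3 (so 19.5% on treatment), and a further 15% to 30% of patients in each arm with only non-serious added events. If every centre took the wide reading, the ratio would be (19.5 + 15)/(15 + 15) = 1.15 to (19.5 + 30)/(15 + 30) = 1.10. If half the patients were at such centres, it would be (19.5 + 7.5)/(15 + 7.5) = 1.20 to (19.5 + 15)/(15 + 15) = 1.15. In all four cases the absolute difference stays at 4.5 percentage points, for example 34.5 − 30. Only the ratio moves, with some loss of precision. Even that direction assumes the added events are balanced between arms, which need not hold if treated gastric symptoms are drug-related.

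It is also fair to say that the primary endpoint is untouched: its components are defined and adjudicated separately (sections 4.1.2, 6.1 and 6.2). Section 9.2.4 sets out no SAE-specific test.

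**Conclusion.** The point holds as a conflict inside an operative definition. Section 7.2 gives SAE two meanings that select different events, sections 7.3 and 4.2 depend on the term, and no text resolves the choice. The balance of the protocol favours the seriousness list, so the consequence is a possibility: SAE counts could mix serious and non-serious events, and some sites could expedite events that others do not. This rests only on the wording and on the assumption that at least some sites might follow the opening sentence. The protocol supplies no basis for a size. The problem concerns safety reporting and tabulation, and is worth correcting because the term carries an expedited duty and the repair is small.

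**What to change.** Reconcile the two paragraphs of 7.2 so that SAE refers only to the seriousness criteria wherever it appears in 4.2, 7.2 and 7.3. Then choose one of two routes for the opening sentence:

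1. Delete it.
2. Keep the category under a different name, for example other significant adverse events, with its own abbreviation and a separate table. State whether the laboratory part is an additional route into the category or a further condition, and say that the 24-hour rule of 7.3 does not refer to this category.

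The cost is a one-sentence protocol correction and a notice to sites. Sample size and the primary efficacy analysis do not change. If sites have already reported under the present text, recorded SAEs should be checked against the seriousness criteria, blind to treatment, before database lock.

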# 7.2.1 . Definition on specificity of serious adverse events

In this study, the following events will not be reported as serious adverse events unless they are judged negative and the researcher believes that it is related to the study drug

- Cardiovascular death
- Re-hospitalization for heart failure
- Given up treatment due to worsening heart failure
- Successful resuscitation after cardiac arrest
- Malignant arrhythmia
- Non-fatal stroke

Other events leading to fatal outcomes should be reported as serious adverse events.

